#### 2.8.2. Measurement Tools

Table 4 demonstrate the measurement tools that will be used at each timepoint. Although one timepoint is sufficient for determining the feasibility of collecting the data by researchers, there are other uncertainties that can be addressed by using two timepoints. Collecting data at both timepoints will allow us to assess the acceptability of the study design by estimating the burden of taking part in the measurements for children and also the ELC educators supporting the data collection. Additionally, we will be able to estimate potential programme effects and determine which child health outcomes should be taken forward as primary and secondary outcomes in a powered effectiveness evaluation.

#### Demographic Questionnaire

At baseline, parents/carers of participating children will be asked to complete an online demographic questionnaire to describe their family background (child’s date of birth, gender identity, ethnic identity, number of siblings, double or single parent household, age of mother when child was born), as well as how many hours per week the child spends at their ELC setting and their home postcode. The postcode will be used to calculate the level of multiple deprivation experienced at the local area level where the child lives as defined by the Scottish Index of Multiple Deprivation (SIMD) [52]. The SIMD is a composite measure of education, crime, health, income, and housing to develop an estimate of area-based deprivation for all neigbourhoods in Scotland. The SIMD scores for participating ELC settings will also be calculated. 

#### Strength and Difficulties Questionnaire (SDQ)

Emotional and behavioural wellbeing will be measured using the validated parent-reported SDQ [53,54]. The parent-reported SDQ was chosen rather than the teacher-reported SDQ to reduce the burden on participating ELC settings. The SDQ has 25 items divided into 5 scales with 5 items each: emotional symptoms, conduct problems, hyperactivity/inattention, peer relationship problems, and prosocial behaviour. Parent/carers will be asked how true different statements are about their child on a 3-point scale ranging from 0 (not true) to 2 (certainly true). The total difficulties score is calculated based on all the scales excluding the prosocial scale to give a score between 0 and 40. An online version of the SDQ will be completed before the study exposure period commences and at the end of the study exposure period (follow-up).

#### Height and Weight

Children will have their height and weight measured at baseline across all participating ELC settings (to the nearest 0.1 cm/kg). Weight status will be presented as a BMI z-score. Children in the fully outdoor and traditional ELC setting will also have their height and weight measured at follow-up.

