2. To what extent can ***propensity score matching*** based on multiple treatment groups be suitably applied within this context?	Data collected on number of children successfully matched across all participating ELC settings.	Children’s demographic information used for matching.	Observed covariates are recorded in both groups. A propensity score is calculated based on these characteristics. Propensity score of children in fully outdoor settings and satellite settings will be matched with propensity score of children in traditional ELC settings. The difference in average outcomes of the matched pairs are compared and a local average treatment effect is estimated. To reduce the risk of bias, matching will be combined with difference-in-differences method, facilitates correction of differences between groups that are fixed over time (reduces the risk of bias in the estimation).	Participating children in all participating ELC settings in Glasgow.	Average treatment effect will be calculated based on the propensity scoring matching of participants from each group.
3. What ***outcomes*** should be included in a future impact evaluation and how should they be measured?	Data collected on outcome measurements using, device worn measurements, questionnaires, and observations. Completeness of data collected and ease of use regarding measurement tools. Which outcome measurement tools identify a change in effect from baseline to follow-up (positive, negative, or null)?	Weight and height: portable standiometer and digital scales. Motor competence: Preschool Gross Motor Quality Scale (PGMQS)PA and sleep: Axivity device. Social and emotional outcomes: strength and Difficulties Questionnaire (SDQ). Play: Tool for Observing Play Outdoors (TOPO). Semi-structured interviews.	Baseline: weight and height, PGMQS, Axivity (7 days with a minimum of 3 full consecutive days), SDQ. TOPO will be implemented during exposure period. Follow-up: weight & height, PGMQS, SDQ, Axivity. Semi-structured interviews with managers and practitioners. Parents will be given a questionnaire at the end of the study asking how the SDQ and Axivity measurement tools were received.	Participating ELC settings in Glasgow, children, staff, and parents/carers.	Summary statistics will be presented for the outcome measures, means and standard deviations will be presented.

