2. To what extent can propensity score matching based on multiple treatment groups be suitably applied within this context?	GREEN: 80% or more enrolled children suitably matched based on propensity scores. AMBER: 50–79% enrolled children matched. RED: less than 50% enrolled children matched.	GREEN: Strong indication that matching children based on their propensity score is a reliable comparison method to be used in a powered effectiveness evaluation. AMBER: Indication that the matching method might work in an effectiveness evaluation; however, it should be considered alongside other criteria such as the level of missing data. RED: The study design method needs careful consideration before being used again.	Determine the suitability of the covariates collected in the demographic survey are sufficient to calculate reliable propensity scores for matching.	We consider 80% to be achievable if the criteria regarding retention in RQ1 is successful.
3. What ***outcomes*** should be included in a future impact evaluation and how should they be measured?	GREEN: 70% or more measures are returned fully completed at baseline and follow-up. Outcome measures are able to identify a change from baseline to follow-up and a difference in effect between intervention and comparison groups (positive or negative). No major acceptability issues during educator interviews or via parent feedback. AMBER: Outcome measure completion rate of 60% or more. An indication that there may be a difference in effect but insufficient data to determine definitively. Three or four major acceptability issues raised by interviewees or through parent feedback; however, mitigating strategy identified. RED: Less than 60% of outcome measures completed. Major acceptability issues raised regarding measurement methods with no possible mitigation strategy.	GREEN: Strong indication to proceed with the outcome measurement methods. AMBER: Medium indication to proceed. Recommend discussing the measurement methods with research steering group. RED: Indication of doubt as to whether to proceed. Measurement methods should be discussed with steering group, taking into consideration findings from RQ6 and whether different measurement tools might be better suited to detect an effect in outcomes.	Baseline and follow-up outcome measures. Feedback from parents in activity diary. Process evaluation interviews with ELC educators.	We consider 70% completion rate sufficient to carry out analysis.

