6. To what extent is the ***study design acceptable*** to ELC managers and practitioners?	GREEN: analysis of interview data identifies little (minor) to no barriers on supporting the study design within the constructs of the NPT. AMBER: three or four modifiable barriers identified within the constructs of NPT. RED: several major and non-modifiable barriers identified regarding the acceptability of the study design among interviewed participants within the constructs of NPT.	GREEN: Strong indication that the study design methods are acceptable among early years educators and children and can be taken forward to a powered effectiveness evaluation. Recommendation as per green target of RQ2. AMBER: Indication that the interview responses should be discussed with the research steering group and a decision made on how the study design can be adapted to be less burdensome. Recommendation as per amber of RQ2. RED: Indication that study design is too labour intensive for participants and needs to be revised before progression to next stage of the evaluation. Recommendation as per red of RQ2.	Acceptability of the study design will be assessed through interviews with ELC headteachers/managers and practitioners using the four constructs of NPT (Coherence, Cognitive Participation, Collective Action, Reflexive Monitoring) as part of the process evaluation. See Appendix A for the interview guide.	A focus on major issues associated with the constructs of NPT is considered acceptable for qualitative data rather than quantitative targets.

**Table 4 ijerph-19-07461-t004:** Outcome measurement methods for the feasibility and pilot study.

Participant	Measurement Tool	Data Collection Timepoints at Participating ELC Settings		
		Baseline (Week 0)	Mid-Point	Follow-Up (Week 5)
Child	Parent/carer Demographic Questionnaire	🗴		
	Strength and Difficulties Questionnaire	🗴		🗴
	Height and weight	🗴		🗴
	Preschool Gross Motor Quality Scale	🗴		🗴
	Axivity (physical activity, sedentary time, sleep)	🗴		🗴
Headteachers/ practitioners	Play behaviours (TOPO)		🗴	🗴
	Semi-structured interviews			🗴
	ELC Monitoring and evaluation tools	🗴		

**Table 5 ijerph-19-07461-t005:** Balance tasks using the preschool gross motor quality scale (adapted from Sun et al., 2010).

Task Code	Balance Task	Criterion Code

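### Section 2.8.2 omits satellite children from follow-up height and weight while Tables 1 and 4 do not, and TOPO has no baseline although RQ3 GREEN asks for one

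*Protocol article*

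**What the plan says.** **Height and weight.** The section 2.8.2 paragraph opens with all models: "Children will have their height and weight measured at baseline across all participating ELC settings". It then narrows: "Children in the fully outdoor and traditional ELC setting will also have their height and weight measured at follow-up". No reason is given for leaving out satellite settings. The RQ3 row of Table 1 has no such limit: "Follow-up: weight & height, PGMQS, SDQ, Axivity". Table 4, under the column heading "Data Collection Timepoints at Participating ELC Settings", marks height and weight at week 0 and at week 5, again for every model.

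**TOPO.** The RQ3 row of Table 1 lists it among the outcome tools: "Play: Tool for Observing Play Outdoors (TOPO)". On timing, the same row says "TOPO will be implemented during exposure period", and its baseline and follow-up lists both omit TOPO. Table 4 marks TOPO at mid-point and week 5. Neither table gives a baseline.

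**The rule.** For RQ3, the GREEN level in Table 3 begins "70% or more measures are returned fully completed at baseline and follow-up". It also asks that outcome measures show a change between the two time points and a difference between intervention and comparison groups, with no major acceptability issues. AMBER needs a completion rate of at least 60%; below 60% is RED.

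**The concern.** A researcher at a satellite setting in week 5 cannot follow both section 2.8.2 and the tables. Because the paragraph moves from all settings to two named models, the second sentence does not read as shorthand for everyone.

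Satellite is one of the two exposure groups in section 2.2, each to be matched with traditional children. The RQ2 row of Table 1 combines matching with difference-in-differences, which needs both time points. If the week 5 measurement is skipped, one of the two planned BMI contrasts is lost and cannot be recovered later.

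TOPO raises a related problem. A tool scheduled without a baseline is to be graded by a rule that asks for one. Its grade would then reflect the schedule and say nothing about whether the tool is workable or acceptable. The study's stated aim is to decide on progression against these criteria, so the rule should be one that each tool can be tested on.

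**Working it through.** The protocol gives no sample size or power calculation to reproduce. The 70% is a decision threshold, so the check compares schedules and takes simple proportions.

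**1. Schedules side by side**

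| Measure | Source | Baseline | Mid-point or exposure period | Week 5 |
|---|---|---|---|---|
| Height and weight | Section 2.8.2 | all models | – | fully outdoor and traditional only |
| Height and weight | Table 1, RQ3 | yes | – | yes, no model excluded |
| Height and weight | Table 4 | yes | – | yes, no model excluded |
| TOPO | Table 1, RQ3 | no | exposure period | not in the follow-up list |
| TOPO | Table 4 | no | mid-point | yes |

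The tables include satellite children by not excluding any model; they do not name them.

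**2. BMI contrast if section 2.8.2 is followed**

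Difference-in-differences for satellite versus traditional is (satellite follow-up − satellite baseline) − (traditional follow-up − traditional baseline). The first term is missing, so the contrast cannot be estimated at any sample size or under any denominator. For fully outdoor versus traditional, all four terms are present.

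**3. BMI completeness under section 2.8.2 (illustration)**

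Inputs from section 2.6: two settings per model and at least 10 children per setting, so at least 6 × 10 = 60 children. Assumptions: the rule is applied per measure and all enrolled children form the denominator.

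- Equal recruitment, perfect data: 40/60 = 66.7%, below 70% and in the AMBER completion band.
- Equal recruitment, 80% retention (the RQ1 GREEN level): 0.8 × 40/60 = 53.3%, in the RED band.
- Same, under the tables' schedule with perfect data: 60/60 = 100%.

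Ten per setting is a minimum, so the split between models can move. With perfect data, completeness equals 1 − s, where s is the satellite share, and 1 − s ≥ 0.70 requires s ≤ 30%. With 20 satellite children, 47 others suffice: 47/67 = 70.1%.

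| Children per setting (fully outdoor / satellite / traditional) | Completeness with perfect data |
|---|---|
| 10 / 10 / 10 | 66.7% |
| 12 / 10 / 12 | 70.6% |
| 10 / 10 / 20 | 75.0% |
| 10 / 15 / 15 | 62.5% |
| 10 / 20 / 10 | 50.0% |

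At 80% retention the condition tightens: 0.8 × (1 − s) ≥ 0.70 gives s ≤ 12.5%, so 20 satellite children would need at least 140 others.

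**4. Other readings of the 70% rule**

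- Only scheduled measurements counted: 40/40 = 100%.
- Pooled over the four before-and-after tools (height and weight, PGMQS, SDQ, Axivity) at 60 children: (3 × 60 + 40)/(4 × 60) = 220/240 = 91.7%.
- Pooled with TOPO added at zero: 220/300 = 73.3%.

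All three pass.

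**5. TOPO**

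With no baseline there are no baseline and follow-up pairs, whatever the sample size, and no change from baseline can be computed. Read per measure, both GREEN clauses fail by design. The per-measure reading fits the purpose: section 2.8 says RQ3 is to identify which outcomes and tools go forward, and section 2.8.1 considers measures for progression according to whether they detect a signal. A single pooled percentage could not choose among tools.

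**The case against.** The strongest reply is that little here is fixed. A reader might infer that two outcome measures cannot reach GREEN even with perfect data. For height and weight the documents do not support that. It would need four things together: section 2.8.2 prevailing over both tables, the rule applied per measure, all enrolled children in the denominator, and satellite children above 30% of the sample. Nor is the signal part of GREEN blocked, since fully outdoor versus traditional can still be assessed. This part of the reply stands.

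It can also be said that section 2.8.1 describes the criteria as graded levels, not strict cut-offs, that AMBER and RED lead to steering group discussion, and that interview and parent feedback are weighed too. The team would see a gap caused by its own schedule. That is fair: an automatic markdown of either measure is not established. It does not bring back an unmeasured follow-up.

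On TOPO, section 2.8.2 describes a place-based tool recorded by play event and used to test whether the full form can be completed. It is not described there as a before-and-after measure for each child, so a figure of 0% baseline completeness should not be read as a data failure. This narrows the point, but Table 1 lists TOPO under RQ3 and Table 3 makes no exception for it.

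**Conclusion.** The point holds as an internal inconsistency; no arithmetic in the protocol is wrong.

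- **Firm:** section 2.8.2 conflicts with Tables 1 and 4 on follow-up height and weight in satellite settings. If section 2.8.2 is followed, one of the two planned BMI contrasts cannot be estimated.
- **Firm on a per-measure reading:** TOPO cannot satisfy the GREEN clauses on baseline completion and change from baseline. The two tables also differ on whether it is part of the week 5 follow-up.
- **Conditional:** the 67% and 53% figures for BMI illustrate equal recruitment with a per-measure rule and all enrolled children counted. They are not limits set by the design.

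The correction should be made before data collection, because a missed follow-up measurement is permanent.

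**What to change.** 1. In section 2.8.2, change the follow-up sentence so that height and weight are measured at follow-up in all three models, as Tables 1 and 4 already schedule.
2. In the RQ3 row of Table 3, judge TOPO on completeness of its scheduled observations and on acceptability, without the baseline and change-from-baseline clauses.
3. Make TOPO's timing the same in Tables 1 and 4.
4. In the same RQ3 row, state whether the 70% applies per measure or pooled, and whether the denominator is all enrolled children or only those scheduled for the measurement.

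The cost is one sentence in section 2.8.2 and short edits to the tables. In the field it adds a small amount of measurement time per satellite child, at the visit already planned for the follow-up PGMQS.

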#### Preschooler Gross Motor Quality Scale (PGMQS)

Some research suggests that exposure to play and learning in nature-based ELC may have a greater benefit on certain motor skills than play and learning at traditional ELC settings alone. These associations could be more applicable to gross motor and vestibular skills, rather than object control [10]. Development of these motor skills provide the foundation for more specialised movements that can influence long-term PA levels. In our stakeholder workshops, the ELC practitioners identified several activities that are popular among children attending outdoor nature-based settings such as climbing and managing obstacles such as trees or those built by children themselves. These require important motor skills such as the ability to balance. This study will apply the balance assessment of PGMQS, a validated tool for use in 3-year-olds that assesses four components of balance: single leg standing, tandem standing, walking line forward, and walking line backward [52]. This tool has previously been used to investigate balance development in preschoolers taking part in an outdoor loose parts intervention in Nova Scotia [55]. One child will be assessed at a time; the researcher will demonstrate how to correctly perform the task and then ask the child to perform the task. They will have one practice trial followed by two scored trials. Each balance task is composed of 4 or 5 criteria as outlined in Table 5. Each criterion will be scored a 0, indicating the movement performed incorrectly, or 1, indicating the movement performed correctly, to get a total balance score out of 18. The two scored trials will be added to give a total score out of 36. Measures will be collected at baseline and follow-up (5 weeks).

#### Physical Activity, Sedentary Time, and Sleep

Children’s physical activity, sedentary time, and sleep will be measured using a wrist-worn triaxial accelerometer (Axivity AX3). Wrist-worn devices have been found to be more acceptable and less burdensome compared with hip-worn devices [56]. Preliminary piloting of the Axivity devices with a small sample of 3-year-olds for 3 days has found high levels of acceptability and compliance. Children will be asked to wear the activity monitor on their non-dominant wrist to limit miscalculated activity counts during sedentary behaviours (e.g., drawing, writing, and playing on mobile electronic devices) [57]. The devices will be configured to record raw acceleration data using Open Movement GUI (OMGUI, V1.0.0.43). Parents/carers will be asked to ensure that their child wears the device for 7 days (24 h/day) with a minimum of 3 consecutive days, removing it only if it causes discomfort or when the child is in water (e.g., swimming or bathing). Parents/carers will be provided with an activity diary to log any time the device is removed from their child’s wrist, the reason why, and the time it is placed back on their child’s wrist. The devices will be programmed to start at the end of the day when anthropometric measures and motor skills assessment are completed. Age-appropriate cut points will be applied to the data to identify activity intensities. Physical activity intensity cut points vary depending on the type of activity monitor used (e.g., ActiGraph, GENEActive, Axivity), the location on the body where it is mounted (e.g., wrist, waist, or thigh), and the age group of the study population. There is not yet a consensus regarding a standard approach to analysing PA by accelerometer [58,59]. Moreover, Axivity monitors have not yet been validated in the preschool-aged population [60]. Research suggests that due to the sporadic activity pattern of preschool-aged children, shorter epoch lengths (5-s epoch) at a sampling frequency of 100 Hz may be more suitable to identify very short periods of movement [61]. Therefore, based on recent research using wrist-worn accelerometers with preschoolers, our PA intensity thresholds are: sedentary behaviour, ≤221 counts per 5-s epoch; light PA, 222–729 counts per 5-s epoch; MVPA ≥ 730 counts per 5-s epoch; and total PA ≥ 222 [62]. These cut points have been used in wrist-worn accelerometers in a similar Scottish ELC setting [63]. The light sensor on the Axivity monitor is a logarithmic lux sensor (a measure of the intensity of light) that has a wavelength characteristic similar to the human eye. It is recommended that the AX3 monitor is calibrated at 1000 lux [64].

Sleep will be estimated by calculating the sleep period time (SPT) frame, the time window from initial sleep onset and waking up after the last sleep episode of the night, based on z-angle variance [65,66]. Using this, the average time of sleep onset and waking (beginning and end of SPT window) will be calculated. The total period of continuous inactivity periods (no change in z-angle of >5° for a minimum of 5 min) within the SPT-window will be calculated to estimate sleep duration per night, then averaged across available nights [66]. A minimum wear time of 3 complete days will be required for analysis. There is not yet a standard recommendation for non-wear time among preschool-aged children [61]. Therefore, we will define the device as not being worn if there are 60 consecutive minutes of zero acceleration recorded. This will be cross-checked with the activity logs to identify any non-wear time less than 60 min.

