Children	Three years old at the time of recruitment or turning three during the study period (May to August 2022). Must spend at least three sessions per week (morning or afternoon sessions or all day) at the ELC setting included in the study. Children who have consent from their parents to participate. Specific to satellite settings: children who have attended their satellite outdoor space 3 times or less.	Not three years old at the time of recruitment or will not be three before the end of the study period (August 2022). Spend less than 3 sessions per week at the ELC under study. Have a serious injury or disability (e.g., wheelchair bound, broken leg, restricted arm movement) that would significantly limit their ability to engage in the study measurement methods. Children whose parent/carer does not provide informed consent to take part. Specific to satellite settings: children who have attended their satellite outdoor space more than 3 times.
ELC educators	Practitioners who supervise the children and support their play while outdoors. Managers/headteachers of participating ELC settings.	Practitioners who do not spend their working hours outside with the children when the children are outside (e.g., administrative staff).

**Table 3 ijerph-19-07461-t003:** Study criteria for progression to a powered effectiveness evaluation.

Feasibility and Pilot Study Criteria for Progression to a Powered Effectiveness Evaluation				
Research Question	Traffic light progression criteria	Recommendation if Green, Amber, or Red	Method of assessment	Rationale

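### The accelerometer non-wear rule does not fit the raw signal as written, the count-based cut points have no stated bridge from that signal, and valid wear need not include an ELC day

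*Protocol article*

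**What the plan says.** All the rules are in section 2.8.2 of the protocol article, under Physical Activity, Sedentary Time, and Sleep, unless another place is named.

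- **Signal.** A wrist-worn triaxial Axivity AX3 is used: "The devices will be configured to record raw acceleration data using Open Movement GUI".
- **Non-wear.** "we will define the device as not being worn if there are 60 consecutive minutes of zero acceleration recorded". The diary check follows: "This will be cross-checked with the activity logs to identify any non-wear time less than 60 min". Parents are also asked to log every removal, with its reason and the time the device goes back on.
- **Sleep.** Sleep is taken as sustained inactivity inside a sleep-period window. Inactivity means that the z-angle does not change by more than 5° for at least 5 minutes.
- **Intensity.** Sedentary is up to 221, light 222 to 729 and MVPA 730 or more, all in counts per 5-s epoch. The section itself says "Physical activity intensity cut points vary depending on the type of activity monitor used" and "Axivity monitors have not yet been validated in the preschool-aged population". It adds that these cut points have been used with wrist-worn devices in a similar Scottish setting.
- **Valid wear.** "A minimum wear time of 3 complete days will be required for analysis". Earlier in the section, and in Table 1 (RQ3), parents are asked for seven days with at least three consecutive days. Recording starts at the end of the day on which the anthropometric and motor measures are taken.
- **Attendance.** Table 2 on included children: "Must spend at least three sessions per week", where a session may be a morning, an afternoon or a whole day.

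**The concern.** The non-wear rule is written for a signal that falls to zero when the device is off the wrist. The recorded signal does not. A stationary accelerometer still senses gravity, and the protocol's sleep method depends on that component being present. If the rule does not fire, an unlogged removal looks like stillness: sedentary time by day, sleep inside the night window. The day may also still pass as complete.

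The valid-wear rule raises a second issue. The three models differ in what children do at ELC, yet a recording made up only of days away from ELC is admissible for comparing them.

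These data feed decisions. Table 3 (RQ3) requires 70% or more of measures complete and a difference between groups for GREEN. Section 2.9.3 uses children's physical activity as a covariate for other outcomes, so errors in it would carry over. Choosing the outcomes for the full evaluation is a stated purpose of the study.

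**Working it through.** The plan gives no figure on this point to reproduce. Three checks follow.

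**1. Does a still device read zero?**

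A stationary triaxial sensor was simulated at the protocol's 100 Hz for 60 minutes (100 × 3,600 = 360,000 samples). The documents give no noise figure, so noise SDs of 0, 1, 2.6 and 5 mg per axis were assumed.

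| Assumed noise (mg) | Minimum vector magnitude (g) | Samples exactly zero | 5-s epochs exactly zero after subtracting 1 g (negative values set to 0) |
|---|---|---|---|
| 0 | 1.000 | 0% | 100% |
| 1 | 0.996 | 0% | 0% |
| 2.6 | 0.988 | 0% | 0% |
| 5 | 0.978 | 0% | 0% |

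On the raw reading the rule does not fire at any noise level. Subtracting gravity rescues it only for a noise-free sensor. A zero-count reading could let it fire, but that requires a raw-to-count step that the article does not state. A child lying still in sleep could then also yield zero counts and be removed as non-wear.

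The scale can be illustrated with one unlogged two-hour removal (an assumed length). It adds 120 minutes of false sedentary or sleep time to that day. Averaged over valid days, that is 120/3 = 40 min/day with three days, or 120/7 = 17 min/day with seven.

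**2. Are the cut points in the units of the signal?**

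The signal is acceleration and the thresholds (221 and 730) are counts per 5-s epoch. Nothing in the article links the two. No misclassification rate can be computed from the document.

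**3. Can three valid days contain no ELC day?**

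Inputs: k distinct weekday ELC days; fitting on an ELC day; the next seven full days recorded. Taking k = 2 assumes that three half-day sessions may fall on two days. If exactly three valid days fall at random among the seven, then P(no ELC day) = C(7−k, 3)/C(7, 3), with C(7, 3) = 35.

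| ELC days k | P(no ELC day) | Patterns where any three days can avoid ELC | Patterns where three consecutive days can | Mean share of consecutive runs with no ELC day |
|---|---|---|---|---|
| 2 | 10/35 = 28.6% | 20 of 20 | 20 of 20 | 42% |
| 3 | 4/35 = 11.4% | 30 of 30 | 21 of 30 | 20% |
| 4 | 1/35 = 2.9% | 20 of 20 | 8 of 20 | 8% |
| 5 | 0 | 0 of 5 | 0 of 5 | 0% |

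A pattern is one combination of attended weekdays and fitting day.

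Example: a child attends Monday to Wednesday and is fitted on Wednesday evening. The recording runs Thursday to Wednesday and holds five consecutive 3-day runs. Their ELC-day counts are Thu–Sat 0, Fri–Sun 0, Sat–Mon 1, Sun–Tue 2 and Mon–Wed 3. Two of the five contain no ELC day.

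**The case against.** **Non-wear.** A reader might infer that the rule can never work. The documents do not support that. The same section classifies activity in counts, so zero counts is a possible meaning, and the failure is certain only on the raw reading. Parents are also asked to log removals of any length, which limits the damage to unlogged ones. No frequency of unlogged removal is given, so 120 false minutes every day cannot be claimed. A daytime removal outside the sleep window would not count as sleep. What stands is that the text says acceleration, and that the diary's stated role in the analysis is limited to gaps under 60 minutes.

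**Cut points.** A reader might infer that they are wrong for this device. The article discloses the lack of validation and of consensus, and it cites wrist-worn use in a similar setting. The conversion may sit in a fuller protocol. What stands is that the units differ and the link is unstated.

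**Valid wear.** Seven days are requested, so three is a floor, and many children may exceed it. A reader might take 3/7 = 43% of an ELC-day effect as bias. It is the ceiling on what whole-week averaging retains for a child attending three days, if the effect is confined to ELC days. Whole-week activity is a legitimate outcome. Nor are such children wrongly classed as exposed, since exposure is attendance over the five weeks. What stands is that recordings with no ELC day can enter the between-model comparison.

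**Stage.** This is a feasibility study with exploratory inference, and testing the tools is part of its purpose. That tempers the severity, but Table 3 still ties progression to completeness and a detected difference.

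**Conclusion.** The point holds in a bounded form, and the change should be made.

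- **Non-wear.** On its plain reading, the rule misses removals of 60 minutes or more that are not in the diary, so sedentary time is overstated, or sleep if the removal falls in the sleep window. On the zero-count reading the error may run the other way, with still sleep lost. The document does not settle which reading applies, and the total bias cannot be sized.
- **Cut points.** The bridge from raw acceleration to counts is unstated, and the size of any misclassification cannot be derived.
- **Valid wear.** Children attending two to four days a week can be analysed with no ELC day. The chances of 28.6%, 11.4% and 2.9% describe the minimum case of exactly three randomly placed valid days. They shrink as more days are returned, and five-day attenders are unaffected.

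The article also leaves unclear whether the three days must be consecutive.

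**What to change.** 1. Define non-wear by low variability of the raw signal (SD and range on each axis) over 60-minute windows. Cross-check it with the diary for removals of any length, not only those under 60 minutes.
2. State the raw-to-count conversion used before the cut points are applied, and label the intensity results provisional.
3. Require at least one valid ELC-attendance day for the between-model activity comparison. Report activity during ELC hours alongside the whole-week figure. The attendance records already planned under RQ1 (section 2.8) identify the days.
4. Reconcile the three consecutive days requested in section 2.8.2 and Table 1 with the three complete days required for analysis.

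The cost is some text, changes to the processing script and a little more processing work on raw files that will be held anyway. A few recordings would become invalid. One ELC day in three does not remove the averaging over other days, which is why the ELC-hours summary is needed as well.
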